### Participants and recruitment strategy and randomization

A trained community center staff member will help to generate a list of potential subjects from their membership list. Potential subjects will be called and recruited into the program if they fulfill the following inclusion criteria: (1) aged ≥18 years old, (2) have no cognitive impairment as evidenced by a score of 22 or above in the Hong Kong version of the Montreal Cognitive Assessment (18), (3) can understand and communicate in Cantonese, (4) provide care to older adults aged ≥60 at least 4 h per week for a minimum of 3 months, (5) use a smartphone, (6) know how to access the Internet, (7) commit to attending bi-weekly, 15–30 min online meetings with the program providers over the 3-month period, and (8) are willing to receive individual-specific video messages covering caregiving skills via WhatsApp. They will be excluded if they are (1) known to have serious alcohol and drug problems, (2) are unable to write and read, (3) have mental health problems, and (4) have already participated in other telecare health or social programs. When two or more potential subjects are taking care of the same older adult, only the one who has spent more time with the older adults is allowed to participate.

A trained research assistant (RA) will introduce the program and invite eligible subjects to join the program in the community centers, and obtain verbal consent upon their agreement. After collecting their baseline data, the research assistant will call the principal investigator (PI) of the research team for randomization. The PI will put the numbers generated from a software program called “Research Randomizer” into sealed envelopes (i.e., “1” = intervention group, “2” = control group). These envelopes will be opened sequentially when a call is received from the RA. In this study, the RA and the community center staff will be blinded, but the PI and the healthcare providers will not.

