### Intervention group

Each intervention group subject will receive three intervention components: (1) online nurse case management supported by a health-social partnership team, (2) individual-specific video messages covering caregiving skills sent via WhatsApp, and (3) an online information center and discussion forum via a password-protected, newly-developed caregiver website.Online nurse case management supported by a health-social partnership team

Each intervention group subject will be assigned to a nurse case manager (NCM) during the first week of the program. The NCM has extensive experience in providing care to informal caregivers and has been trained specifically for this program. She will meet with the subjects bi-weekly via Zoom. The time of the meetings will be settled with the agreement of both the NCM and the subjects. In the first Zoom consultation, the NCM will assess the caregiving needs and problems of the subjects by using a structured and validated assessment-intervention-evaluation tool: The Omaha System. The Omaha System consists of 42 problems under four domains ─ environmental, psychological, physiological, and health-related behaviors (19). The NCM will empower the subjects to set goals and develop a personalized care plan tailored to their identified caregiving needs and problems. The goals and care plan will be followed up and revised in subsequent Zoom consultation sessions. The NCM will also provide emotional support, encourage the subjects to discuss their concerns, identify perceived challenges to achieving their goals, and together with the subjects find solutions in the Zoom consultation sessions on how to tackle these barriers. When deemed necessary, based on a jointly developed protocol and the problems of the subjects, the NCM will refer the subjects to one of the health-social partnership team members, which includes social workers, traditional Chinese medicine practitioners, a physiotherapist, and a mental health nurse. The protocol indicates the roles and responsibilities of each member in the health and social team, the suggested assessment, interventions and an evaluation scheme for each member, and the arrangement and logistics of the program. A monthly conference will also be held among the team members to review the referred subjects’ condition, care plans, and goal status.Individual-specific video messages covering caregiving skills sent via WhatsApp

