### Control group

Both intervention and control group participants will receive services from the community centers as usual. The community centers will provide regular onsite educational sessions and workshops for enhancing the caregiving knowledge of caregivers. Attendance at these lectures is not mandatory, and all subjects are welcomed to join.

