### Background demographic data

The background demographic data of the participants will be collected at baseline (T1). The data will include age, gender, marital status, level of education, number of caregiving hours per week, work status, duration of caregiving, financial situation, family structure, person with whom they live, and experience of using a smartphone. See Figure 3.

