## Data processing and analysis

The Statistical Package for the Social Sciences (SPSS) version 26.0 will be used to conduct a statistical analysis. The demographic data of the intervention and control groups will be compared at baseline, using appropriate tests (i.e., Mann–Whitney U, *t*-tests, or chi-square). Depending on the normality of the data, an independent *t*-test or a Mann–Whitney *U* test will be used to determine the group differences in both primary and secondary outcomes in T2. Intention-to-treat will be employed as the primary analysis in this study. Potential covariates, such as the duration of caregiving, the number of caregiving hours per week, and the number of referrals will be examined. Within-group differences will be analyzed using either the Wilcoxon signed-rank test (non-parametric) or a paired t-test (parametric). A significant result is indicated when the *p*-value (level of significance) is less than 0.05 for a two-tailed test.

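### The number of referrals is listed as a potential covariate, but it arises after randomisation and, as described, only in the intervention arm; a between-group model containing it would not estimate the intention-to-treat effect

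*Protocol article*

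**What the plan says.** Protocol article, Data processing and analysis: "Potential covariates, such as the duration of caregiving, the number of caregiving hours per week, and the number of referrals will be examined". The same section says "Intention-to-treat will be employed as the primary analysis in this study", and it names an independent t-test or a Mann–Whitney U test, which "will be used to determine the group differences in both primary and secondary outcomes in T2". It gives no adjusted model.

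Four other places show what a referral is and when it occurs:

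- **Intervention group:** when it is judged necessary, given a jointly developed protocol and the participant's problems, "the NCM will refer the subjects to one of the health-social partnership team members". On who has a nurse case manager (NCM): "Each intervention group subject will be assigned to a nurse case manager (NCM) during the first week of the program".
- **Control group:** "Both intervention and control group participants will receive services from the community centers as usual". No NCM and no referral route is mentioned for controls.
- **Participants and recruitment strategy and randomization:** "After collecting their baseline data, the research assistant will call the principal investigator (PI) of the research team for randomization".
- **Background demographic data:** the T1 list includes "number of caregiving hours per week, work status, duration of caregiving". It does not include referrals.

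**The concern.** A covariate used to adjust a randomised comparison should be fixed before randomisation, so that it cannot be affected by the assigned treatment. Two of the three named variables meet that condition. The number of referrals does not. It is part of the first intervention component, it responds to need that emerges after assignment, and as described it can be non-zero in one arm only.

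If it enters a model comparing the arms, two things can go wrong. Benefit delivered through referral to the health-social team is taken out of the group coefficient, although the article's Discussion presents that team as a strength of the programme. And because referral follows need, intervention participants without referrals are a lower-need subset, who are then compared with controls of every level of need. The first distortion hides a real effect; the second can create or inflate one.

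**Working it through.** **Step 1. Timing and arm.** Baseline data come first, then randomisation, then assignment of an NCM in week 1 to intervention participants, then referrals by that NCM. So referrals come after randomisation. Controls have no NCM, so a count of zero for them is a strong inference, though not stated text.

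**Step 2. What the group coefficient becomes.** Let A be arm, R the number of referrals (R = 0 in controls) and Y the T2 score. In a linear model of Y on A and R, controls determine the intercept and only the intervention arm informs the slope b of Y on R. Therefore

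adjusted group coefficient = (mean Y in intervention − b × mean R) − mean Y in control = unadjusted difference − b × mean R.

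This is the predicted outcome of intervention participants with no referral, minus the mean of all controls. It equals the intention-to-treat difference only if b = 0, that is, if referrals neither affect the outcome nor track prognosis (or if the two happen to cancel).

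**Step 3. Inputs for an illustration.** From the article: 40 per group, and the planning effect size of 0.403, taken here as a true difference of -0.403 SD (a higher score on the stress scale means more stress). Assumed, because the article gives nothing: a mean of 0.5 to 2 referrals per intervention participant; Poisson counts whose log mean rises by 0.5 per SD of need; a need–outcome correlation r of 0, 0.3 or 0.6; and none, half or all of the effect carried by referrals.

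**Step 4. Hand calculation.**

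- *All of the effect carried by referrals, mean 1, r = 0:* b = -0.403, so the coefficient is -0.403 + 0.403 × 1 = 0.00.
- *Half carried, mean 1, r = 0:* b = -0.202, so -0.403 + 0.202 = -0.20.
- *None carried, referrals follow need:* for mean m, var(R) = m + 0.284m² (0.284 = e^0.25 − 1) and cov(need, R) = 0.5m, so b = 0.5r/(1 + 0.284m). With m = 0.5 and r = 0.3, b = 0.15/1.142 = 0.131 and the coefficient is -0.403 − 0.131 × 0.5 = -0.47. With m = 2 and r = 0.6, b = 0.30/1.568 = 0.191 and the coefficient is -0.403 − 0.191 × 2 = -0.79.
- *Standard error (residual SD 1):* √[(2 + m/(1 + 0.284m))/40]. Without referrals it is √(2/40) = 0.22. With them it is √(2.438/40) = 0.25 at m = 0.5 and √(3.276/40) = 0.29 at m = 2.

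**Step 5. Simulation, 40 per arm.** The results agree with the hand calculation.

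| Assumed truth | Without referrals | With referrals |
|---|---|---|
| -0.403, none via referrals, r = 0 | about -0.40 | about -0.40, larger SE |
| -0.403, half via referrals, r = 0 | about -0.40 | about -0.20 |
| -0.403, all via referrals, r = 0 | about -0.40 | about 0.00 |
| -0.403, none via referrals, r = 0.3 to 0.6 | about -0.40 | -0.47 to -0.79 |
| No effect, r = 0.3 to 0.6 | about 0.00 | -0.07 to -0.39 |

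In the last row, the rejection rate at a nominal 5% reaches about 28% (mean 2, r = 0.6). When both mechanisms act, the estimates lie between these extremes, and the two biases may cancel by chance: with half the effect via referrals, r = 0.3 and mean 2, the estimate was -0.405.

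**The case against.** The strongest reply is that the comparison the article describes cannot contain this covariate. Neither a t-test nor a Mann–Whitney U test takes covariates, so the stated primary result stays as it is. The wording is also tentative: covariates are potential and are to be examined, with no model named. That could cover a dose-response look within the intervention arm, which would be legitimate, and an analysis plan that is not shown may say so. The analysis section does not define referrals, and nowhere is it said that controls score zero. The simulated sizes rest on assumed rates and links.

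All of this stands as a limit on the point. A reader might infer that the trial's primary estimate is biased, or that the plan contradicts its own intention-to-treat statement. The text supports neither. A conflict would arise only if a referral-adjusted model were reported as the primary between-group result, and the article does not say that it will be.

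The reply does not remove the defect. This is not a gap left for the analysis plan to fill, but a variable that the article names and puts in the wrong class. Listed as a covariate beside two baseline variables, directly after the intention-to-treat sentence, it permits the adjustment shown above, and nothing in the article restricts it to descriptive or within-arm use.

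**Conclusion.** The point holds in conditional form. As the article describes them, referrals are post-randomisation acts of the intervention and are driven by need, so they do not belong in a list of covariates for comparing the arms. The unadjusted T2 test is unaffected. A between-group model that included referrals would not estimate the intention-to-treat effect, and its standard error would rise, in the illustration from about 0.22 to between 0.25 and 0.29 SD.

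The bias can go either way. Its size cannot be derived from the article: the range of about 0.00 to -0.79 SD around a true value near -0.40 SD depends wholly on the assumed referral rate, the link with need and the share of benefit carried by referral. The conclusion also rests on reading referrals as those made by the NCM and on a control count of in effect zero, which is the natural reading but an inferred one.

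This should be fixed before the analysis. It is a correction to a named variable and does not invalidate the design or the main test.

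**What to change.** Remove the number of referrals from the covariate list. State that any adjustment of the between-group comparison is limited to variables measured at T1, such as the two already named (caregiving duration and weekly caregiving hours). Report referrals descriptively within the intervention arm as a process or dose measure, or in an exploratory analysis that is labelled as such and kept apart from the intention-to-treat comparison.

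The cost is one phrase removed and one sentence added. No data collection, sample size or conduct changes, and the referral counts remain available for the process report.

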### Aim

The aim of the study is to evaluate the effectiveness of a telecare-based intervention on stress levels in informal caregivers of older adults.

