### Data collection

Data will be collected at two time points – pre-intervention (T1) and post-intervention (T2). The data will be collected through phone call by a trained RA. Five percent of completed questionnaires (i.e., 4) will be randomly selected for an independent review to ensure the quality of the collected data.

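### Within-arm before-after tests share the p<0.05 rule with the between-group test and are given no subordinate role, although they cannot answer the effectiveness question

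*Protocol article*

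**What the plan says.** The Aim section sets out to "evaluate the effectiveness of a telecare-based intervention on stress levels in informal caregivers of older adults". Under Data collection, "Data will be collected at two time points – pre-intervention (T1) and post-intervention (T2").

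The section Data processing and analysis then gives two kinds of outcome test:

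- Between groups: an independent t-test or Mann-Whitney U test "will be used to determine the group differences in both primary and secondary outcomes in T2".
- Within groups: "Within-group differences will be analyzed using either the Wilcoxon signed-rank test (non-parametric) or a paired t-test (parametric").

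The next and last sentence of that section is the decision rule: "A significant result is indicated when the *p*-value (level of significance) is less than 0.05 for a two-tailed test". It names no test and excludes none.

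The only statement about what is primary in the analysis is "Intention-to-treat will be employed as the primary analysis in this study". That settles who is analysed and in which arm. It does not say which of the two kinds of test carries the conclusion.

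On background care, the Control group section states: "Both intervention and control group participants will receive services from the community centers as usual".

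**The concern.** The question is whether telecare added to usual services lowers stress more than usual services alone. Only the randomised contrast answers it. A paired test inside the intervention arm has a different null hypothesis, namely that the arm's mean (or median) did not change between T1 and T2. That null can be false when telecare does nothing, because the arm also lives through three months and keeps access to the centres' educational sessions and workshops.

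Setting the two paired tests side by side does not repair this. A p-value below 0.05 in one arm and above 0.05 in the other is not a test of the difference between the arms.

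Because one rule labels every p<0.05 a significant result, a report that follows the plan could list a significant fall in PSS in the intervention arm with the same standing as the randomised comparison. At stake is how the result is read. The between-group test itself and its type I error are untouched.

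**Working it through.** The plan states no figure for the within-arm tests, so there is none to reproduce. The check asks how often these tests give p<0.05 when the intervention has no effect.

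**Inputs from the protocol article**
- Two-sided alpha 0.05 (Data processing and analysis; Sample size).
- 34 evaluable people per arm (Sample size). This agrees with 40 randomised per arm and 15% drop-out: 40 × 0.85 = 34. Whether 34 follows from the stated effect size is a separate matter and is not used here.
- One primary and four secondary outcomes, so at least 5 × 2 = 10 within-arm tests if each outcome gives one score.

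**Assumptions (not in the documents)**
- No true intervention effect.
- Both arms improve by the same amount c, in SD units, with c from 0.2 to 0.5.
- T1-T2 correlation r from 0.5 to 0.7, and equal SD at T1 and T2.

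**Formulas**
- The SD of the change is √(2(1−r)), so the standardised change is dz = c / √(2(1−r)).
- p = power of the paired t-test, from the noncentral t distribution with 33 degrees of freedom and noncentrality dz × √34.
- The arms are independent, so the chance that the intervention arm is significant and the control arm is not is p(1−p). This cannot exceed 0.25, its value at p = 0.5.
- Between-group test under no effect: 0.05 / 2 = 2.5% in the direction favouring the intervention.

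**Worked example, c = 0.3**
- r = 0.5: dz = 0.3 / √1.0 = 0.300; noncentrality 0.300 × 5.831 = 1.75; p = 0.397; p(1−p) = 0.397 × 0.603 = 0.239.
- r = 0.7: dz = 0.3 / √0.6 = 0.387; noncentrality 0.387 × 5.831 = 2.26; p = 0.592; p(1−p) = 0.592 × 0.408 = 0.242.

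**Results at 34 per arm**

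| Shared change c (SD) | r | dz | Intervention arm p<0.05 | Intervention yes, control no |
|---|---|---|---|---|
| 0.2 | 0.5 | 0.200 | 0.205 | 0.162 |
| 0.2 | 0.7 | 0.258 | 0.310 | 0.214 |
| 0.3 | 0.5 | 0.300 | 0.397 | 0.239 |
| 0.3 | 0.6 | 0.335 | 0.476 | 0.249 |
| 0.3 | 0.7 | 0.387 | 0.592 | 0.242 |
| 0.5 | 0.5 | 0.500 | 0.808 | 0.155 |
| 0.5 | 0.7 | 0.645 | 0.955 | 0.043 |

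With no change over time (c = 0), the within-arm rate is the nominal 5%, and a significant improvement in the intervention arm only occurs in 2.4% of trials.

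**Check by simulation** (20,000 trials per scenario, r = 0.5, 34 per arm, no effect). At c = 0.2 the intervention-arm test was significant in 20.1%, and in that arm only in 15.8%. The two-sided between-group test rejected in 4.8%. At c = 0.403 (a value inside the range) the figures were 62.9%, 23.6% and 5.2%.

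**Sensitivity to n.** With all 40 per arm analysed, the intervention-arm rate runs from 23.5% (c = 0.2, r = 0.5) to 97.8% (c = 0.5, r = 0.7).

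**The case against.** The best defence is that the section gives the two kinds of test different jobs. The between-group test is the one assigned to group differences in the primary and secondary outcomes; the paired tests only describe whether an arm changed, which they do validly. The p<0.05 sentence is a generic threshold, and a paired p<0.05 is a significant change over time, not a significant effect of telecare. The ranking of tests may also sit in a fuller protocol or SAP that is not shown.

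Much of this stands. A reader might infer that the protocol intends to claim effectiveness from the intervention arm's own change, or from contrasting the two arms' p-values. No sentence says so, and the allocation of tests points the other way. What does not fall away is that the article itself chose these tests, put them under the same rule and gave them no lower standing. An unseen document does not change that wording.

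Three further inferences should be resisted:

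- That a null between-group test beside a significant intervention-arm change is the likely outcome because power is low. This depends on the metric of the 0.403 effect size, which the Sample size section does not state. At 34 per group, power is about 37% if it is Cohen's d and about 91% if it is Cohen's f (d = 0.806).
- That regression to the mean drives the change. Eligibility sets no minimum stress score, so the documents give little support for it; time and usual services suffice.
- That 24-25% is the typical rate of the discordant pattern. It is the ceiling of p(1−p), and the rate is 4% at one end of the assumed range.

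**Conclusion.** The point holds in a limited form. The plan puts within-arm tests under the same significance rule as the randomised comparison and does not subordinate them, although they do not estimate the effect named in the aim. It does not state that they will be read as effectiveness, so this is an ambiguity that invites a misreading, not an invalid primary analysis.

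Under the assumptions set out (no true effect, shared improvement 0.2 to 0.5 SD, correlation 0.5 to 0.7, 34 per arm), the intervention-arm test is significant in about 20-96% of trials. The intervention-only pattern occurs in about 4-25%, against 2.5% for the between-group test in that direction. These rates depend on a shared change over time whose size the documents do not give; without such a change the within-arm test keeps its nominal 5%. The wording should be changed, but the matter is moderate in weight.

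**What to change.** Rewrite the analysis paragraph as follows:

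1. Replace the paired t-tests and Wilcoxon signed-rank tests with a descriptive report, per arm, of T1, T2 and mean change with 95% confidence intervals and no p-values.
2. State that effectiveness is judged only on the between-group difference in PSS at T2, adjusted for T1 PSS. The adjustment alone would not cure this point, since the within-arm tests and the open rule would remain. It does put the T1 data to use in the comparison that matters.
3. Apply the p<0.05 rule to between-group comparisons only, with PSS as the primary outcome and self-efficacy, depression, quality of life and caregiving burden as secondary. Restricting the rule to PSS alone would take the threshold away from the planned between-group secondary tests, which this point does not call for.

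The cost is a rewording. T1 PSS is already collected, no data are added, and at least ten fewer tests are run.
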